### Recruitment

The research coordinator at each study site will oversee recruitment. Estimated time for the recruitment phase will be 9 months, with the aim of recruiting 100 participants total. Potential participants are screened through PC clinics (primarily urology or radiation oncology) at each site and approached based on initial medical record review by the research coordinator. Potential participants are provided with a brief description of the study, and given an opportunity to ask any questions. If they are interested in study participation, written informed consent is obtained and a baseline assessment will be scheduled.

### Assessments

Participants complete five assessments in total: at baseline, three months, six months (end of intervention), nine months, and twelve months. The nine- and twelve-month assessments provide follow-up information after completion of the active intervention. Blinded outcome assessments are conducted by a Certified Exercise Physiologist (CEP; Canadian Society of Exercise Physiology, CSEP) or Registered Kinesiologist.

### Baseline assessment

The baseline assessment consists of obtaining socio-demographic and clinical data as well as assessing fitness using measures of resting heart rate (HR), blood pressure (BP), oxygen saturation, body composition (body mass index, waist circumference and body fat percentage), upper-lower body strength testing, and cardiovascular testing (peak VO2). Participants also complete questionnaires (see below) and are scheduled for a bone mineral density (BMD) test (if one has not been completed in the last year) and blood work (fasting glucose, prostate-specific antigen (PSA), testosterone, hemoglobin, and cholesterol profile). Serum is also banked for ancillary studies on participants at the Toronto site. All measures are detailed below and summarized in Table 1.

**Table 1 Tab1:** **Summary of study measures at specified time points**

Domain/Measure	Time required	T_0_: (Baseline)	T_1_: (3 mo.)	T_2_:6 mo. (End Int.)	T_3_: 9 mo. (3 mo. f/u)	T_4_:12 mo. (6 mo. f/u)
**Quality of life**						
FACT-G (primary)	8-10 min	●	●	●	●	●
FACT-P	4-5 min	●	●	●	●	●
FACT-F	5 min	●	●	●	●	●
**Physical Fitness**						
VO_2_Peak	20 min	●	●	●	●	●
Sit-to-Stand test	1 min	●	●	●	●	●
Grip Strength	1 min	●	●	●	●	●
**Biological Outcomes**	<5 min	●		●		●
Blood glucose						
Cholesterol profile						
PSA (safety)						
Testosterone						
Hemoglobin (covariate)						
**Body Composition**						
Bone mineral density	30 min*	●				●
Body composition$	5 min	●		●		●
**Adherence**						
Accelerometer	**-**	●	●	●	●	●
GLTEQ	<5 min	●	●	●		
Sessional attendance#	-					
**Adherence Predictor Variables**						
NEWS-A	10 min	●	●	●	●	●
HCCQ	5 min	●	●	●	●	●
BREQ2	5 min	●	●	●	●	●
ROPAS	5 min	●	●	●	●	●
PAB questionnaire	5 min	●	●	●	●	●
Sedentary Behaviours	5 min	●	●	●	●	●
**Cost-Effectiveness**						
Health questionnaire	5 min	●	●	●	●	●
EQ-5D	5 min	●	●	●	●	●
**Study Completion**	5 min					●

*****Can be done on separate day to reduce participant burden.

$Includes waist circumference, waist circumference:height ratio, and % body fat using bioelectrical impedance analysis.

#Only for those in supervised groups (done weekly).

***Abbreviations****:**BREQ2* Behavioral Regulations in Exercise Questionnaire – 2, *EQ-5D* EuroQol 5 dimensions of health scale, *FACT-G* Functional Assessment of Cancer Therapy General, *FACT-F* Fatigue subscale, *FACT-P* Prostate subscale, *GLTEQ* Godin Leisure Time Exercise Questionnaire, *HCCQ* Health Care Climate Questionnaire, *Int* Intervention, *NEWS-A* Neighborhood Environment Walkability Scale short form, *PAB* Planning, Attitudes, & Behavior questionnaire, *PSA* prostate-specific antigen, *ROPAS* Relatedness to Others in Physical Activity scale, *VO2 Peak* Peak Volume of Oxygen Consumption.

### Assessments (three, six, nine and twelve months)

All follow-up assessments include updates on clinical data, fitness measurements, and self-report questionnaires. BMD testing occurs only at baseline and twelve months, blood work and body composition testing is done only at baseline, six months and twelve-months (Table 1).

### Objective measures/ Primary and secondary outcomes

#### Body composition

Body composition is measured following the CSEP’s [26] Canadian Physical Activity Training for Health [27] assessing waist circumference (WC), weight, waist to hip ratio (WHR), body mass index (BMI). Body fat percentage (BF%) is measured via bioelectrical impedance analysis (BIA) using the Tanita TBF-300A device (Illinois, USA). Additionally, participants receive a BMD scan of the lumbar spine, total hip, and femoral neck using dual x-ray absorptiometry.

### Fitness testing

Prior to the start of fitness testing, resting HR, BP, and oxygen saturation are measured. Aerobic fitness is directly assessed through the modified Bruce treadmill protocol (treadmill-based graded exercise test) [28], which assesses volitional peak oxygen consumption (VO_2_ peak) using a metabolic cart (Parvo Medics TrueOne 2400 Metabolic Measurement System). Lower body strength is measured with a one minute sit-to-stand test [29,30] and grip strength is used to assess upper body strength. Grip strength is measured with a Jamar dynamometer averaging three readings obtained in each hand [31].

### QOL and fatigue

Functional Assessment of Cancer Therapy – General (FACT-G) is used to assess general health-related QOL [32], whereas the FACT-P (Functional Assessment of Cancer Therapy - Prostate) evaluates prostate-specific QOL [33] and the FACT–F (Functional Assessment of Cancer Therapy – Fatigue) is used to evaluate cancer-related fatigue [34]. All three questionnaires are validated and have been widely used in cancer research measures, and in particular, in RCTs of exercise in men on ADT [14].

### Biological outcomes (blood data collection)

At three assessment time points (baseline, 6 months and 12 months), participants’ blood is drawn to analyze fasting blood glucose, lipid profile (total cholesterol, low density lipoprotein, high density lipoprotein, and triglycerides), testosterone, as well as PSA levels. Blood glucose and lipids are being monitored as ADT is associated with an increased risk of both diabetes and dyslipidemia [35,36]; conversely, exercise is associated with improvements in both metabolic parameters [37]. PSA levels are being monitored as a safety measure [38], as in other exercise trials [10,12,39], and testosterone is measured to assess adequacy of castration.

### Adherence

Program adherence and predictors of adherence are assessed. Adherence measures include physical fitness outcomes (as the most proximal, objective outcome of exercise adherence), accelerometry, as well as attendance at exercise sessions (for those in supervised programs). For those in the home-based, smartphone-assisted arms, use of the self-report software (Connected Wellness Platform, NexJ Systems, Toronto, Canada) and interview responses (obtained by health coaches) will provide proxies for attendance and exercise program engagement. Accelerometers (Actigraph GT3X, Pensacola, FL) will be worn for seven days at each assessment time point. Accelerometers will be worn during waking hours, allowing for capture of total physical activity during the observation period [40]. Data will be extracted from the accelerometer in 60-second epochs and will be screened through; (i) at least 4 days of valid data, including (ii) at least 10 hours of wear time per day; (iii) non-wear time will be assessed as periods of time with no movement (0 counts per minute) for more than one hour at a time.

Two common definitions of adherence are adopted: 1) at least 150 minutes of MVPA per week, based on the ACSM guideline for cancer survivors [28] and the revised CSEP guideline for adults and older adults [41]; and 2) at least 10,000 steps per day [42] for 6+ days per week. In a sensitivity analysis, a recently described age-specific cut-off of 7,500 steps per day for older adults [43] is also tested. The accelerometer data will be analyzed by examining the total amount of MVPA and sedentary behavior during the 7 days. MVPA is defined as activity >1952 counts per minute [42] and sedentary behaviour as <100 counts per minute and time spent inclined.

Predictors of adherence are targeted based on a social ecological framework (Figure 1) [44]. Multiple potential determinants of exercise adherence and the inter-relatedness of these determinants are examined using brief validated measures at each level: exosystem (Neighborhood Environment Walkability Scale: Short Form (NEWS) [45]); mesosystem (Health Care Climate Questionnaire [46] and Related to Others in Physical Activity Scale [47]); and microsystem (Behavioral Regulations in Exercise Questionnaire-2 [48,49] and a Planning, Attitudes, & Barriers scale [50,51]).

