### Study population/participants

Men diagnosed with histologically confirmed PC of any stage, starting or continuing on ADT for at least 6 months (or who remain biochemically castrate after stopping ADT), able to speak, read and write in English, and living in close proximity to either study center are eligible for the study. Each potential participant is screened with the Physical Activity Readiness questionnaire (PAR-Q+ or PARmed-X) [24] and/or receives physician approval. If an individual already meets the American College of Sports Medicine (ACSM) guidelines for moderate to vigorous physical activity (MVPA) or has a condition that would interfere with his ability to participate (e.g. severe arthritis limiting ambulation, major neuropsychiatric abnormality, severe visual/hearing loss, poorly controlled pain), he is excluded from the study.

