### Statistical analysis

Statistical analysis focuses on feasibility outcomes and those which will inform decisions about moving forward to and planning a phase III clinical trial. Feasibility outcomes include recruitment rates, and proportions of participants retained and adherent at landmark times throughout the study, all of which will be estimated with 95% confidence intervals. Additionally tallies are kept on reasons for not participating. Each participant also completes an exit interview and satisfaction survey which will be analyzed for participant satisfaction within the study and cost effectiveness analysis.

Adherence is assessed through the two different binary definitions given previously, based on steps or hours of exercise. We estimate proportions adhering to exercise in each three-month period and use generalized estimating equation logistic regression models to compare adherence between groups and assess predictors of adherence over the course of the study. Predictors include sociodemographic (e.g. age, education), clinical (disease stage), baseline fitness, and ecological variables (NEWS, etc.).

Quality of Life (FACT-G and FACT-P), musculoskeletal fitness, and aerobic fitness are efficacy outcomes that are analyzed using linear mixed effects model with subject-specific random effects and group-by-time interactions. The analysis will not focus on differences between groups, but, to assist with phase III trial design, estimation of measures of within and between-person variance.

As previously mentioned, there is no formal cost-effectiveness analysis, however data obtained (diary and EQ-5D completion and participant acceptance) is used to help develop this outcome for the phase III study. Descriptive estimates of costs by category and per intervention arm as well as per site (Toronto, Calgary) will be calculated.

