### Criteria to move forward to phase III RCT

To move forward to the phase III intervention, we have identified pre-specified criteria which must be met during the phase II study. Reasonable recruitment (at least 25% of potentially eligible approached participants), adherence (70%) and retention rates (70%), at least moderate satisfaction of participants, and capture of at least 80% of clinical outcomes collected are the minimum criteria. The intention is that all three of the interventions will move forward to the phase III study; however, if one arm proves to be inferior to the other two, based on adherence, retention, satisfaction or QOL and physical fitness results, then only two will move to phase III.

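### Entry does not screen on steps and the adherence model does not name the baseline accelerometer value, so a man who met the step definition before training can later count as adherent

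*Protocol article*

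**What the plan says.** - **Entry (Study population/participants).** A man is excluded if he "already meets the American College of Sports Medicine (ACSM) guidelines for moderate to vigorous physical activity (MVPA". Steps are not mentioned, and the article does not say how activity is measured at screening.
- **Definition 1 (Adherence).** "at least 150 minutes of MVPA per week, based on the ACSM guideline for cancer survivors [28". It draws on guidelines from the same body as the exclusion.
- **Definition 2 (Adherence).** "at least 10,000 steps per day [42] for 6+ days per week". For the sensitivity analysis, "a recently described age-specific cut-off of 7,500 steps per day for older adults [43] is also tested".
- **Measurement (Adherence; Table 1).** Accelerometers "will be worn for seven days at each assessment time point", and Table 1 marks baseline (T0) as one of these. MVPA is activity above 1952 counts per minute.
- **Analysis (Statistical analysis).** Adherence is analysed through these two binary definitions. Proportions are estimated for each three-month period, and GEE logistic models compare the arms and assess predictors. "Predictors include sociodemographic (e.g. age, education), clinical (disease stage), baseline fitness, and ecological variables (NEWS, etc".
- **Decision (Criteria to move forward to phase III RCT).** Adherence of 70% is one of the minimum criteria, and an arm that proves inferior on adherence, among other results, may be left out of phase III. The section does not say which adherence measure the 70% refers to.

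**The concern.** The entry rule and the two adherence definitions do not match. The MVPA exclusion is meant to keep out men who already satisfy definition 1. Nothing does the same for definition 2. Steps taken below 1952 counts per minute do not count as MVPA, so a man who walks a great deal at low intensity can be eligible and already satisfy definition 2 at T0. The 7,500-step version would include at least as many such men. If he carries on as before, he is counted as adherent.

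Adherence and its predictors are one of the trial's stated aims, and adherence feeds the decision to proceed. Two things are at stake.

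- **Comparison and predictor models.** Prior activity is likely to be a strong determinant of later step status. If it is left out, the arm comparison loses precision. A predictor such as neighbourhood walkability may then pick out men who already walked, not men who took up the programme.
- **The 70% figure.** If it is judged on steps, it mixes uptake with prior habit.

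**Working it through.** **The plan's own figure.** The target is 90 men (30 per arm) with 10% drop-out: 90 / (1 − 0.10) = 100. This matches the stated recruitment of 100. No power calculation is stated, so there is no other figure to reproduce.

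**Inputs.** From the article: 90 men in total, 30 per arm, and a 70% adherence criterion. Assumed: a share *b* of entrants meets the step definition at T0, and all of them still meet it later. The article gives no value for *b*, so it is varied from 0% to 20%. Let *q* be uptake among the other men.

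**Step 1. Uptake that yields an observed 70%, if the criterion is read on steps.** Observed adherence = b + (1 − b)q. Setting this to 0.70 gives q = (0.70 − b) / (1 − b).

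- b = 5%: 0.65 / 0.95 = 68.4%
- b = 10%: 0.60 / 0.90 = 66.7%
- b = 20%: 0.50 / 0.80 = 62.5%

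**Step 2. Chance of reaching the criterion when true uptake is 60%.** The criterion is 63 of 90 (70%). The observed probability is p = b + 0.60(1 − b), and the upper tail is binomial with n = 90.

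| b | p | P(at least 63 of 90) |
|---|---|---|
| 0% | 0.60 | 3.2% |
| 5% | 0.62 | 7.1% |
| 10% | 0.64 | 14.1% |
| 20% | 0.68 | 38.9% |

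**Step 3. Arm comparison.** Allocation is randomized after the baseline assessment, so the expected difference in *b* between arms is zero. The SD of the chance difference between two arms of 30 is √(2b(1 − b)/30).

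- b = 5%: √(2 × 0.05 × 0.95 / 30) = 5.6 percentage points
- b = 10%: √(2 × 0.10 × 0.90 / 30) = 7.7 points
- b = 20%: √(2 × 0.20 × 0.80 / 30) = 10.3 points

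Men who are adherent whatever their arm also dilute a real difference in uptake by the factor (1 − b). A 20-point difference becomes 0.90 × 20 = 18 points at b = 10% and 0.80 × 20 = 16 points at b = 20%.

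**The case against.** Several counter-arguments have force.

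- **The predictor list is open-ended.** It is introduced as a set of examples, the document is a journal article, and an analysis plan not shown may list baseline activity. This stands: the article does not rule the covariate out. It does, however, fix the entry rule and the outcome definitions, and it names baseline fitness where baseline activity is the closer match. Fitness is only a partial proxy for daily steps.
- **Definition 1 is largely covered by the exclusion.** This stands. A reader might infer that both definitions are open to prior adherers, for instance through under-reporting at screening. The article gives no evidence of that.
- **Randomization protects the arm comparison.** This stands. A reader might infer that the comparison credits prior habits to one arm. It does not do so systematically, and chance imbalance is already reflected in the standard error of an unadjusted comparison. The gain from adjustment is precision.
- **The 70% is not tied to steps.** This stands. The Adherence section also lists attendance, app use, coach interviews and fitness. If the criterion means attendance, the inflation does not arise in this way. If it means definition 1, the exclusion largely prevents it. Against that, attendance is recorded only in the supervised arms, so an accelerometer reading is plausible for a criterion covering all three.
- **The baseline share is assumed.** This stands. The Discussion describes most men on ADT as inactive, which lends no support to the upper end of the range. At 5% the effect on the criterion is small.
- **An absolute guideline level is a legitimate target for a feasibility trial.** This stands too, and is a reason not to redefine the criterion.

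**Conclusion.** The point holds for the step definition and its 7,500-step version. Entry does not screen on steps, the definition is an absolute level, and the T0 accelerometer value is collected but not among the predictors named for the adherence model.

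The consequence for the arm comparison is limited to chance imbalance (SD about 6 to 10 points for an assumed *b* of 5% to 20%, at 30 per arm), some dilution and lost precision. The predictor analysis is exposed to confusing prior walking with uptake.

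A reader might conclude that the 70% criterion is inflated. The document supports this only conditionally: the criterion would have to be read on steps, some entrants would have to meet the step definition at T0, and they would have to go on meeting it. The size cannot be fixed from the document. This is a worthwhile and nearly free improvement to the analysis, not a flaw that undermines the trial.

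**What to change.** 1. In the adherence GEE, include the T0 accelerometer value as a baseline covariate: steps for definition 2, MVPA minutes for definition 1. State that the outcomes are the T1 to T4 assessments.
2. Report, by arm, the proportion meeting each definition at T0, including the 7,500-step version.
3. State which adherence measure the 70% criterion uses. Keep the criterion on all men as pre-specified, and show adherence among men not adherent at T0 beside it as a supplementary figure.

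The cost is wording and one extra table, since the T0 accelerometer week is already scheduled. The small downside is that men without valid T0 wear need a stated handling rule in the adjusted model. A valid record needs only 4 days, while definition 2 needs 6 or more, so T0 step status cannot be established for a man with 4 or 5 valid days. Mean daily steps as a continuous covariate avoids that problem in the model. The supplementary figure will rest on a somewhat smaller denominator.

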### Sample size calculation/power

Following standard guidelines for a phase II RCT [58-60], we have targeted 30 patients per arm (90 patients in total) to provide precise estimates of parameters related to the primary outcomes as well as important feasibility information that will be crucial to inform the phase III study. Assuming 10% drop-out, we will recruit 100 patients across both sites.

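### Accelerometer sedentary time is summarised as a seven-day total with no stated wear-time correction, so it depends materially on how long the device was worn

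*Protocol article*

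**What the plan says.** All of the relevant text is in the Adherence section of the protocol article.

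- **Wear period.** Accelerometers "will be worn for seven days at each assessment time point", in waking hours only. Table 1 lists the accelerometer at all five assessments.
- **Validity screen.** A record needs "i) at least 4 days of valid data, including (ii) at least 10 hours of wear time per day".
- **Non-wear.** The rule is that "non-wear time will be assessed as periods of time with no movement (0 counts per minute) for more than one hour at a time".
- **Sedentary definition.** The article defines "sedentary behaviour as <100 counts per minute and time spent inclined".
- **Summary.** "The accelerometer data will be analyzed by examining the total amount of MVPA and sedentary behavior during the 7 days".

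Neither this section nor Statistical analysis mentions a mean per valid day, scaling to seven days, a percentage of wear time or a wear-time covariate. In Statistical analysis the device data enter through the adherence definitions: "Adherence is assessed through the two different binary definitions given previously, based on steps or hours of exercise". Sedentary time is in neither definition.

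**The concern.** A device worn in waking hours can credit sedentary minutes only in time classed as wear. A total over a fixed week therefore combines two things: how sedentary the man was while observed, and how long he was observed. The screen sets a floor on observation but does not equalise it, and the stated summary does nothing further.

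At stake is the description of sitting across five wear weeks and three arms, two of those weeks falling after the programme has ended. If wear slipped at later visits, or differed between arms, the total would move with no change in behaviour. The document gives no wear data, so this is a risk and not a forecast.

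**Working it through.** The document states no figure for wear hours or sedentary hours, so there is no figure of its own to reproduce on this point. The sample size is not an input.

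**Inputs from the Adherence section:** 7 planned days; at least 4 valid days; at least 10 h on each.

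**Assumed inputs:** full waking wear of 14 to 16 h a day, with 15 h as the central value; a sedentary share of wear time of 65%; only valid days counted in the total.

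**Formula:** recorded total = valid days × hours per day × sedentary share.

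1. *Range of accepted wear.* Minimum: 4 × 10 = 40 h. Full week: 7 × 14 = 98 h to 7 × 16 = 112 h. The ratio is 98/40 = 2.45 to 112/40 = 2.8.
2. *Same behaviour at the two ends.* 0.65 × 40 = 26.0 h, against 0.65 × 7 × 15 = 68.3 h. The first is 40/105 = 38% of the second. These are the extremes, not a typical pair.
3. *One valid day lost.* 6/7 = 0.857, so the total falls by about 14%. This holds at any sedentary share if hours per day are unchanged. If minutes from the rejected day were kept, the fall would be smaller.
4. *Shorter days, all seven valid.* (7 × 13)/(7 × 15) = 91/105 = 0.867, so the total falls by about 13%. Scaling by the number of valid days alone would not remove this.
5. *Ranking can reverse.* A man sedentary for all of 40 observed hours has the same total as a man sedentary for 40/98 = 41% of 98 h, or 40/112 = 36% of 112 h.
6. *Share of variance due to wear.* A simulation took a mean share of 65%, a between-man SD of 5, 8, 10 or 12 percentage points, and about 14 h a day with SD 1.2. The squared correlation of the total with wear time was:

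| Valid days | Variance explained by wear |
|---|---|
| spread evenly over 4 to 7 | 58–89% |
| 65% of men have all 7 | 42–80% |
| 90% of men have all 7 | 29–69% |
| all men have 7 | 17–53% |

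Wear explained more than half in 9 of the 16 scenarios.

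7. *Opposite direction.* The non-wear rule catches zero-count runs only when they exceed one hour. A shorter removal gives zero counts, which is below 100, so it may be counted as sedentary unless the inclination condition excludes it. One such removal a day could add up to 7 × 1 = 7 h to the week.

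**The case against.** The strongest reply is that nothing of consequence rests on this variable. Sedentary time is absent from both adherence definitions, from the efficacy outcomes in Statistical analysis and from the criteria for moving to phase III. Table 1 also lists a separate five-minute Sedentary Behaviours measure at every assessment, apparently a questionnaire, which would not depend on device wear. This stands, and it limits the point to a descriptive result. It does not repair the accelerometer summary.

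A second reply is that a condensed article leaves data processing to the fuller plan. That would answer silence, but the article names both the summary and the window, and a plan that follows the sentence inherits the problem. A fuller plan may still add a standardisation.

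A reader might infer three stronger things that the document does not support:

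- *That the total is mostly a measure of wear.* This depends on spreads the document does not give. Under the assumed inputs the share of variance runs from 17% to 89%.
- *That poorer wear always reads as less sitting.* Longer removals and lost days push the total down, but removals of an hour or less may push it up.
- *That coach contact would create an arm difference in wear at 9 and 12 months.* Health coach support describes weekly contact for four months and fortnightly contact for the last two, within the intervention. No arm-specific contact is described afterwards, and all arms share one assessment schedule.

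**Conclusion.** The point holds as a defect in one stated summary. At an unchanged sedentary share, the seven-day total moves in proportion to recorded wear: about 14% for one lost valid day of seven, and about 13% for 13 rather than an assumed 15 h a day. Accepted records can differ in wear by a factor of 2.45 to 2.8 if a full waking day is 14 to 16 h. The proportionality is arithmetic. The waking-day length, the 65% share and the variance figures are assumptions, and the absence of a correction is read from this article alone.

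The consequence is confined to descriptive sedentary results, which would be distorted if wear differed by visit or arm. It is worth correcting because the remedy is nearly free, not because the trial's main conclusions are threatened.

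**What to change.** In the Adherence section, replace the seven-day total for sedentary behaviour with sedentary time as a percentage of valid wear time. Sedentary minutes per valid day, with wear minutes as a covariate, would serve equally well. Tabulate valid days and wear hours by arm and visit beside it.

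The cost is about one sentence and one table. Wear time already has to be derived for the validity screen, so no new data and no added participant burden are involved.

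There are two limits. The share assumes that unworn waking time resembles worn time; if men take the device off for evening sitting, the share is biased too, and the wear table lets a reader judge how far that could matter. Nor does the change deal with short removals counted as sedentary, which should be noted as a limitation of the one-hour rule.
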